## Abstract

**Background:**

Women’s College Hospital, Toronto, Canada, offers specialized ambulatory surgical procedures. Patients often travel great distances to undergo surgery. Most patients receiving ambulatory surgery have a low rate of postoperative events necessitating clinic visits. However, regular follow-up is still considered important in the early postoperative phase. Increasingly, telemedicine is used to overcome the distance patients must travel to receive specialized care. Telemedicine data suggest that mobile monitoring and follow-up care is valued by patients and can reduce costs to society. Women’s College Hospital has used a mobile app (QoC Health Inc) to complement in-person postoperative follow-up care for breast reconstruction patients. Preliminary studies suggest that mobile app follow-up care is feasible, can avert in-person follow-up care, and is cost-effective from a societal and health care system perspective.

**Objective:**

We hope to expand the use of mobile app follow-up care through its formal assessment in a randomized controlled trial. In postoperative ambulatory surgery patients at Women’s College Hospital (WCH), can we avert in-person follow-up care through the use of mobile app follow-up care compared to conventional, in-person follow-up care in the first 30 days after surgery.

**Methods:**

This will be a pragmatic, single-center, open, controlled, 2-arm parallel-group superiority randomized trial comparing mobile app and in-person follow-up care over the first month following surgery. The patient population will comprise all postoperative ambulatory surgery patients at WCH undergoing breast reconstruction. The intervention consists of a postoperative mobile app follow-up care using the quality of recovery-9 (QoR9) and a pain visual analog scale (VAS), surgery-specific questions, and surgical site photos submitted daily for the first 2 weeks and weekly for the following 2 weeks. The primary outcome is the total number of physician visits related to the surgery over the first 30-days postoperative. The secondary outcomes include (1) the total number of phone calls and emails to a health care professional related to surgery, (2) complication rate, (3) societal and health care system costs, and (4) patient satisfaction over the first 30 days postoperative. Permutated-block randomization will be conducted by blocks of 4-6 using the program ralloc in Stata. This is an open study due to the nature of the intervention.

**Results:**

A sample of 72 (36 patients per group) will provide an E-test for count data with a power of 95% (*P*=.05) to detect a difference of 1 visit between groups, assuming a 10% drop out rate. Count variables will be analyzed using Poisson regression. Categorical variables will be tested using a chi-square test. Cost-effectiveness will be analyzed using net benefit regression. Outcomes will be assessed over the first 30 days following surgery.

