A societal perspective will be adopted wherein all costs are assessed irrespective of the payer [22]. This perspective was chosen based on the US Panel on Cost-Effectiveness in Health and Medicine recommendations. This recommendation is meant to improve comparability and consistency across studies [23]. Furthermore, while a broad societal perspective will be adopted, results will also be presented using a narrower health system perspective that may be of key interest to health administrators and policy decision makers. This alternative perspective focuses on costs borne within the health system and excludes external costs as well as costs borne by patients and their caregivers.

Currently, there are no validated questionnaires that capture patient satisfaction with postoperative care. We have created a post-pilot survey that captures patient satisfaction with the care and information received. All answers are recorded using a 5-point Likert scale (Multimedia Appendix 1). We will also use the QoR-9 scores and VAS recorded at 4 weeks postoperative. Psychometric properties of the QoR-9 include convergent validity and discriminant construct validity. There is also good interrater agreement and internal consistency [24]. The test-retest reliability was 0.61 (*P*<.001). The preferred cut-off is 0.7; however, the QoR-9 was still favored over the QoR-40 due to its ease of use (<2 minutes required to complete the survey) [24].

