Patient satisfaction will be measured at 4 weeks after surgery using the post-pilot survey (Multimedia Appendix 1). The study coordinator will administer this over the telephone. The QoR-9 scores will be recorded at 4 weeks after surgery using the mobile app at home or a tablet during a scheduled clinic visit, depending on the patient’s study arm.

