## Results

### Data Analysis Plan

Descriptive statistics (frequencies, means, standard deviations) will be calculated for all clinical and outcome variables. All data obtained in this study will be entered into Excel and analyzed using Stata 13.

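### The chi-square rule for categorical variables makes no exception for ordered answers, yet it is the only named test that fits the 5-point Likert satisfaction outcome

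*Protocol article*

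**What the plan says.** The Results paragraph of the abstract gives a rule for each type of outcome: "Count variables will be analyzed using Poisson regression"; "Categorical variables will be tested using a chi-square test"; "Cost-effectiveness will be analyzed using net benefit regression". The chi-square sentence is general. It names no outcome and does not separate ordered from unordered categories.

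The Methods paragraph of the abstract lists four secondary outcomes, the last being "4) patient satisfaction over the first 30 days postoperative". Secondary Outcomes describes the instrument: "All answers are recorded using a 5-point Likert scale". Measuring Outcome Variables fixes the time: "Patient satisfaction will be measured at 4 weeks after surgery using the post-pilot survey".

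In the body, the Data Analysis Plan promises that "Descriptive statistics (frequencies, means, standard deviations) will be calculated for all clinical and outcome variables". It is followed by Poisson regression for visits, net benefit regression for cost-effectiveness, and best-case and worst-case handling of missing data. The body does not mention chi-square, and no rank-based, ordinal or continuous-outcome test appears anywhere in the article.

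**The concern.** A Likert answer is neither a count nor a cost, so of the three stated rules only the chi-square rule can cover it. Chi-square treats the five answers as unordered labels: shuffle the columns of the table and the statistic does not change. The question, however, is directional: are app patients more or less satisfied than patients seen in person? A 2x5 chi-square spends 4 degrees of freedom where an ordinal test spends 1, and it estimates nothing.

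The Conclusion of the article names patient satisfaction among the possible ramifications of replacing visits, so the result is likely to be read as evidence on acceptability. A non-significant chi-square from a small trial could be taken as no difference when an ordinal analysis of the same answers would have shown a shift and its size.

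**Working it through.** **Inputs from the article.** Sample Size gives 32 evaluable patients per arm and 36 enrolled (32/0.9 = 35.6, rounded up to 36). These numbers come from the primary outcome: an E-test of 2 versus 1 visits at 32 per arm has 95.2% power one-sided (91.1% two-sided), so the stated 95% reproduces on a one-sided basis. That is a separate matter. No power, effect size or answer distribution is given for satisfaction. The only level reported is the pilot's 3.9/5.

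**Assumptions.** Control answers 1 to 5 have probabilities (.03, .07, .20, .37, .33). The mean is .03 + .14 + .60 + 1.48 + 1.65 = 3.90. The app arm has every cumulative odds multiplied by a common odds ratio (OR). Tests are two-sided at 0.05.

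Example of the shift at OR 3: the probability of answering 5 has odds .33/.67 = 0.493; times 3 this is 1.478, a probability of .596. The same step for 4 or above gives .70 to .875, for 3 or above .90 to .964, and for 2 or above .97 to .990. The app mean is 1 + .990 + .964 + .875 + .596 = 4.43.

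**Sparsity.** With equal arms, the expected count in a cell is half the column total, so it falls below 5 when fewer than 10 patients in all choose that answer: 10/64 = 15.6% or 10/72 = 13.9% of patients. With no difference between arms and 64 patients, answers 1 and 2 have expected column totals of 64 × .03 = 1.9 and 64 × .07 = 4.5. That makes 4 of 10 cells (40%) too small, against the usual limit of 20%. Across three assumed control shapes with mean 3.9, between 93% and 100% of simulated trials broke that limit.

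**Simulated power.** Pearson chi-square (empty columns dropped) against the tie-corrected Wilcoxon rank-sum test, with 4,000 trials per setting at 32 per arm and 40,000 at 36:

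| OR | App mean | 32 per arm: chi-square / Wilcoxon | 36 per arm: chi-square / Wilcoxon |
|---|---|---|---|
| 1.5 | 4.11 | – | 8% / 15% |
| 2 | 4.25 | 16% / 32% | 18% / 35% |
| 2.5 | 4.35 | 27% / 48% | 32% / 54% |
| 3 | 4.43 | 39% / 63% | 44% / 69% |
| 4 | 4.53 | 61% / 83% | 66% / 86% |

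Across the three shapes the Wilcoxon gain at OR 2 to 4 is about 14 to 25 points. With a strong ceiling (control mean 4.58) it falls to 12 points at OR 2. At OR 1.5 it is about 6 to 7 points. With no true difference, chi-square rejects in 3.0% to 4.7% of trials and Wilcoxon in 4.8% to 5.1%.

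**Shifts that are not proportional** (32 per arm):

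| Pattern | Control | App | Chi-square / Wilcoxon |
|---|---|---|---|
| Polarising | .03, .07, .20, .37, .33 | .10, .12, .08, .20, .50 | 46% / 10% |
| Only from 4 to 5 | .03, .07, .20, .37, .33 | .03, .07, .20, .12, .58 | 51% / 26% |
| Low answers move to 4 | .05, .10, .25, .35, .25 | 0, .03, .10, .60, .27 | 49% / 39% |

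Here the advantage reverses, by 10 to 36 points (up to 41 points at 36 per arm).

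**The case against.** The strongest reply is that the article never says satisfaction will be tested by chi-square. The sentence is general, the complication outcome is a natural target for it, and the list of methods is visibly incomplete: QoR-9 and pain VAS scores are collected at 4 weeks and have no named test. The pilot's satisfaction was reported as a mean score, and means and standard deviations are promised for all outcomes, so a numeric analysis may be intended. The survey and any separate analysis plan are not shown.

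Much of this stands. A reader might infer that the plan expressly prescribes chi-square for satisfaction; it does not. What remains is a stated rule for categorical variables with no exception for ordered answers, and a secondary outcome that fits no other stated rule. That is a fault in the rule as written, not merely a detail left to another document.

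Four further inferences go too far:

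- **A fixed loss of 14 to 25 points.** It depends on an assumed proportional shift and an assumed distribution. The gain is smaller at OR 1.5 and reverses in the patterns above.
- **A real difference would usually be missed because of chi-square.** At OR 4 chi-square already detects 61% at 32 per arm, and at OR 2 and 2.5 Wilcoxon also misses more often than not (32% and 48% power).
- **The report would hide which arm did better.** The planned frequencies and means would show direction. What would be missing is an estimated effect with its uncertainty.
- **Sparse cells make the test invalid.** The simulated false-positive rate is at or below 5%; in these settings the test is somewhat conservative.

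Finally, the 3.9/5 is pilot app users' satisfaction with the device and app. It is not a figure for the in-person arm and serves here only to place an illustrative distribution.

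**Conclusion.** The point holds in limited form. The chi-square rule suits binary and unordered outcomes and is a poor choice for the one secondary outcome recorded on an ordered 5-point scale. If it is applied item by item at 32 to 36 per arm, the test ignores order, yields no effect estimate and will nearly always be sparse.

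The power cost is conditional: about 14 to 25 points for a consistent shift with OR 2 to 4, about 6 to 7 points at OR 1.5, and a gain rather than a cost for some polarising or single-step shifts. These numbers rest on assumed distributions and effects and should be quoted only as illustration. An ordinal method is still the better default, because a consistent move up or down the scale is the natural question and because it provides an estimate. The point concerns a secondary outcome with no power target and leaves the primary analysis untouched.

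**What to change.** Restrict the chi-square sentence to binary and unordered variables, and allow an exact test where counts are low. Complications need this: at the 4% rate quoted in the article, 36 patients give 0.04 × 36 = 1.4 expected events per arm.

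Add one sentence for satisfaction: each Likert item is compared between arms with the tie-corrected Wilcoxon rank-sum test, or with proportional-odds regression on study arm. Report the common odds ratio, or the probability that an app patient is the more satisfied of a randomly chosen pair (ties counted as half), with its 95% confidence interval, alongside the frequencies already planned.

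The cost is that sentence. It needs no new data, patients or staff, and both methods are standard in Stata. The downside should be stated openly: sensitivity is lower, in some patterns much lower, to differences that are not proportional, such as polarised answers or movement between two adjacent answers only. The frequency table would show these, though without a formal test.

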**Conclusions:**

We hope to show that the use of a mobile app in follow-up care minimizes the need for in-person visits for postoperative patients.

**Trial Registration:**

Clinicaltrials.gov NCT02318953; https://clinicaltrials.gov/ct2/show/NCT02318953 (Archived by WebCite at http://www.webcitation.org/6Yifzdjph).

## Introduction

### Background and Rationale

Women’s College Hospital (WCH) in Toronto offers specialized surgical procedures, including breast reconstruction following mastectomy for breast cancer. The goal of surgery is to restore a breast mound and improve quality of life in survivors [1-3]. Patients often travel significant distances after choosing to undergo surgery at WCH. Increasingly, telemedicine is used to overcome the distance patients must travel to receive specialized care. Telemedicine is the use of medical information exchanged from one site to another via electronic communication to improve patients’ health status [4].

Several countries with large rural populations have utilized telemedicine services to improve access to care. In India, telemedicine is used to follow postoperative patients with parathyroid disease and thyroid disease. Many of these patients live more than 1000 kilometers away from the tertiary hospital [4]. In Ecuador, a mobile surgical program utilizes telemedicine to provide routine preoperative and postoperative care and demonstrated improved resource utilization through elimination of redundant examinations and superfluous travel [5]. These studies demonstrate that it is possible to improve access to necessary services with cost- and time-savings to patients and providers.

Currently, Women’s College Hospital is using a mobile app (QoC Health Inc, Toronto) to replace in-person follow-up care after surgery for breast reconstruction patients. A feasibility pilot study evaluating the quality of recovery at home using this mobile device has been completed. Preliminary findings suggest that mobile follow-up care adequately detects postoperative complications and is potentially cost effective from a health system perspective [6,7].

Breast reconstruction is an underused option, despite its well-known psychosocial benefits in breast cancer patients [2,8]. Recent studies suggest that low income and nonurban residence are associated with decreased rates of breast reconstruction [9]. Telemedicine data suggest it can join patients and providers separated by physical distance at a reduced cost to society [10-12]. By reducing costs to society, of which a component represents costs borne by patients, we hope to improve access to breast reconstruction among breast cancer survivors.

### Knowledge to Date

#### Why Is Telemedicine an Important Initiative in Ontario?

The Ontario government has devised an action plan to change health care delivery so that it meets the fiscal challenges and needs of an aging population [13]. The Ontario Action Plan identifies technology as an opportunity to reduce the growth in health care costs and eliminate the barrier of distance. The action plan states that Ontarians should have access to the right care, at the right time, in the right place. This project speaks directly to these objectives by providing breast reconstruction patients with timely contact (the right time) with their surgeon (the right care) from the comfort of their home (the right place) [13]. This technology has the potential to address wait times by freeing up specialty surgeon clinic time to see new consults and non-urgent visits to the emergency department by providing direct surgeon contact.

#### Why Is an Elective Ambulatory Population Suitable for Telemedicine Follow-Up?

In general, morbidity and mortality following ambulatory surgery is exceedingly low [14]. This is more apparent in an ambulatory facility where various patient selection rules result in the treatment of largely American Society for Anesthesia (ASA) class I and II patients [14]. These patients are considered healthy or with mild systemic disease, respectively. Complication rates in this subset of breast reconstruction patients are approximately 5% [15]. Low complication rates mean that postoperative intervention is exceedingly unlikely. Previous studies have found that after a tonsillectomy or adenoidectomy, telephone follow-up care with standardized questionnaires is as safe as standard follow-up care and offers considerable cost reduction and patient convenience [16]. Similar telephone follow-up has also been used successfully in elective open hernia repairs and laparoscopic cholecystectomy [17]. Others have shown that planned outpatient appointments after uncomplicated surgery are neither necessary nor cost effective [18]. A “no planned follow-up” saves money for hospitals and patients. However, postoperative follow-up is valued by patients and important for the continuity of care [18]. In this way, telemedicine follow-up care offers a middle ground between conventional in-person follow-up care and no planned follow-up care.

#### Why Use the QoC Health Inc Mobile App?

The QoC Health Inc mobile app allows patients to submit photos and answers to a validated quality of recovery (QoR) questionnaire and Visual Analog Scale (VAS) for the first 30 days postoperative using their mobile device [19]. A feasibility study, including 30 breast reconstruction patients, showed once daily reporting was well tolerated even in the first week postoperative period. There were high levels of satisfaction with the mobile device and app (3.9/5) and low levels of anxiety in knowing that their surgeon was monitoring their recovery [6]. One wound infection and one early dehiscence was picked up using the mobile phone app, leading to immediate intervention. Surgeons were able to follow patient reports on a Web portal. Post-pilot surveys reported an overall positive experience. All patients attended the standard in-person follow-up care visit at 1 and 4 weeks postoperative. Surgeons felt that at least one early follow-up clinic visit could be eliminated when using the remote monitoring technology. This was an unexpected finding [6].

The following proposed catalyst study builds on this pre-existing data by actually eliminating one or more in-person postoperative follow-ups and performs a cost-effectiveness assessment. Demonstrating cost-effectiveness in an elective ambulatory postoperative population would promote its use in similar surgical settings.

### Research Question

In postoperative ambulatory breast reconstruction patients at WCH, can we avert in-person follow-up care through the use of a mobile app compared to conventional, in-person follow-up care in the first 30 days following surgery?

## Methods

### Design Overview

This will be a pragmatic, single-center, open, controlled, 2-arm parallel-group superiority randomized trial comparing mobile app and in-person follow-up care over the first 30 days following surgery. Permutated-block randomization will be conducted by blocks of 4-6 using the program ralloc in Stata statistical software [20].

### Study Setting

All study participants will be recruited from WCH. This has been an exclusively ambulatory hospital since September 2011, meaning that all surgical patients go home the same day or the next day after surgery. The Chief of Surgery (JS) at WCH was instrumental in developing this mobile app and is a champion of eHealth interventions. Due to physician interest, the app will be adapted for use in other surgical patient populations, including arthroscopic orthopedic, thyroid, and parathyroid surgical patients. WCH has the infrastructure to support research and to participate in knowledge dissemination and uptake activities.

### Characteristics of Ambulatory Breast Reconstruction Patients

This patient population is female between 18-70 years of age. Due to the limited availability of breast reconstruction in Ontario [9], patients travel from all over Ontario to receive breast reconstruction. The types of breast reconstruction performed at WCH include immediate (ie, at time of mastectomy) or delayed reconstruction using one-stage reconstruction with alloderm and implants or two-stage reconstruction using expanders that are later exchanged for implants, immediate or delayed reconstruction using a pedicled transverse rectus abdominis myocutaneous flap or pedicled lattisimus dorsi flap, bilateral breast reduction, and fat grafting.

Common indications for breast reconstruction include breast cancer surgery, prophylactic mastectomy due to familial risk factors, and breast hypertrophy qualifying for breast reduction under OHIP (Ontario Health Insurance Plan).

All patients are within the ASA class I, II, and III representing patients with good health, mild systemic disease, and severe systemic disease, respectively. The majority of patients fall within ASA classes I and II. All patients are nonsmokers with a body mass index (BMI) ≤30. Approximately 50% of breast cancer patients receive pre-operative radiation with or without chemotherapy. These factors affect complication rates and therefore determine if the groups are balanced after randomization.

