### Sample Size

The average breast reconstruction patient attends two in-person follow-up visits within the first month after surgery. If we assume that we can avert at least one in-person visit in the mobile app arm and that we have equal number of participants in both groups, we can use the E-test for count data to generate a sample size of 64 (32 patients per group) at a power of 95% (*P*=.05). The E-test is more robust and more powerful than the Conditional test (C-test) originally described to compare two counts. If we assume a 10% dropout rate, we will increase our sample size target to 36 patients per group.

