### Measuring Predictor Variables

Age impacts foregone wage estimates, and postal code impacts travel cost estimates. The type of surgical procedure, ASA classification, BMI, and preoperative radiation impacts rates of successful surgery at 30 days postoperative. Therefore, these variables are considered potential predictors of cost-effectiveness.

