#### Sequence Generation

A block randomization scheme with variable block size will be generated using Stata ralloc [20]. This will ensure approximately equal sample size and that participants and study staff cannot anticipate assignment to either group. Treatments will be allocated in a 1:1 ratio. All study investigators and staff will be blinded to the block number, block size, and sequence in the block. The treatments will be assigned via pre-prepared sealed, opaque envelopes, and the envelopes will be ordered in the sequence of treatment assignments generated by the Stata code. Once eligibility for randomization has been determined, the first available allocation envelope will be assigned to the study subject. The subject will be randomized to the treatment arm indicated inside the envelope.

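### Procedure type is named as prognostic, yet the 72 patients are allocated from one unstratified list; a major/minor stratum would be a cheap improvement

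*Protocol article*

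**What the plan says.** **Case mix.** Under Characteristics of Ambulatory Breast Reconstruction Patients, the eligible operations range from fat grafting and breast reduction to implants, expanders and pedicled flaps. That section ends, after a paragraph on ASA class, smoking, BMI and radiation, with "These factors affect complication rates and therefore determine if the groups are balanced after randomization".

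**Prognosis.** Measuring Predictor Variables includes procedure explicitly: "The type of surgical procedure, ASA classification, BMI, and preoperative radiation impacts rates of successful surgery at 30 days postoperative".

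**Allocation.** Design Overview states "Permutated-block randomization will be conducted by blocks of 4-6 using the program ralloc in Stata statistical software", and Sequence Generation states "A block randomization scheme with variable block size will be generated using Stata ralloc". The sections on intervention assignment describe the 1:1 ratio, the envelopes, and who holds the key. Allocation Concealment has the next envelope drawn from one numbered series. No stratification factor is named anywhere.

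**Analysis.** The abstract gives a chi-square test for categorical variables. The Poisson Regression section compares visits between arms and names no covariate. Only the Net Benefit Regression section brings in procedure, as a binary major/minor term beside study arm, age, distance, BMI and its square, ASA class and radiation.

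**The concern.** The plan treats procedure as prognostic and needs a major/minor classification for one of its models, but does not use that classification at randomisation, where it would cost almost nothing. Checking afterwards whether the arms are balanced describes an imbalance and does not prevent one.

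This matters most for complications, which are the safety check on removing planned visits. With so few events expected, a reader will judge that comparison largely by whether the arms look alike. If one arm visibly holds more flap or implant cases, even a small split in complications is hard to read, and no model can resolve it. For visits, the primary outcome, a prognostic stratum could be used in the analysis, but none is planned.

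**Working it through.** **Inputs**
- Sample size: 32 per group evaluable, 36 per group enrolled (abstract; Sample Size section).
- Visits: two in the control arm, one averted (Sample Size section).
- Complication rate: 4% (Secondary Outcomes; Risks), or about 5% (section on why an elective ambulatory population is suitable).
- Blocks of 4 and 6, 1:1, one list.
- Share of major procedures: not given. Assumed 20%, 30% and 50%.
- Risk ratio for complications, major to minor: not given. Assumed 2 to 5.

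**Step 1. The plan's own sample size.** The plan says "we can use the E-test for count data to generate a sample size of 64 (32 patients per group) at a power of 95"%, starting from "The average breast reconstruction patient attends two in-person follow-up visits within the first month after surgery". An exact E-test for Poisson means of 2 and 1 has power 95.2% at 32 per group with a one-sided 5% level, and 91.1% with a two-sided level. The figure therefore reproduces as a one-sided test. Dropout: 32 / 0.9 = 35.6, rounded up to 36, so 72 in total. The rest of this check uses N = 72.

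**Step 2. Expected complications.** 0.04 x 72 = 2.9, or 0.05 x 72 = 3.6. The chance of five or fewer events is 93% at 4% and 85% at 5%. An arm of 36 has no event with probability 0.96^36 = 23%. A covariate-adjusted model of complications is not workable.

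**Step 3. Chance imbalance with one list.** Probability that the arms differ in their share of major procedures by at least the stated number of percentage points:

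| Share major (assumed) | Method | 10 points | 15 points | 20 points |
|---|---|---|---|---|
| 20% | Simulated blocks of 4 and 6 | 29% | 11% | 3% |
| 20% | Hypergeometric, 14 major | 37% | 13% | 3% |
| 30% | Simulated blocks of 4 and 6 | 36% | 16% | 6% |
| 30% | Hypergeometric, 22 major | 44% | 20% | 7% |
| 50% | Simulated blocks of 4 and 6 | 41% | 20% | 8% |
| 50% | Hypergeometric, 36 major | 48% | 24% | 10% |

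The hypergeometric rows fix 36 per arm and an even number of major cases; the simulation lets that number vary. Ten points of a 36-patient arm is 3.6 patients. With an even total the gap moves in even steps and passes the mark at 4; with an odd total it needs 5. The simulated rows average over both and are therefore lower.

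**Step 4. With two strata.** An incomplete block of 6 leaves at most 3 patients of imbalance per stratum: 3/36 = 8.3 points. No simulated trial with separate lists reached 10 points.

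**Step 5. Effect on the complication comparison.** Let s be the major share and RR the risk ratio, with overall risk 4%. Minor risk = 0.04 / (s x RR + 1 - s), and major risk = RR times that. For s = 0.3 and RR = 3: 0.04 / 1.6 = 0.025 and 0.075.
- A 20-point gap moves 36 x 0.20 x (0.075 - 0.025) = 0.36 expected events. Over s = 20-50% and RR = 2-5 the range is about 0.2 to 0.6.
- The share of variance that stratifying removes is s(1 - s)(difference in risk)^2 / (0.04 x 0.96) = 0.21 x 0.0025 / 0.0384 = 1.4%. Over the same range it is about 0.5% to 3%. If every complication fell in major cases it would be about 4% to 17%.
- The standard error of the rate difference is sqrt(2 x 0.04 x 0.96 / 36) = 4.6 points.

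Gaps in case mix are thus common, but their effect on the complication difference is small beside its sampling error.

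**The case against.** Unstratified permuted blocks are an accepted choice for a single-centre trial of this size. The protocol claims only roughly equal arm sizes and unpredictability for its scheme, and blocking delivers both. The test's standard error already covers chance imbalance. Step 5 shows that the small number of events, not case mix, limits the complication comparison. All of this stands, and it confines the point to an inexpensive improvement.

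Four stronger readings are tempting, and the documents do not support them.
- A reader might infer that the cost-effectiveness result cannot be separated from case mix, because complications are its effect term. The net benefit regression already includes major/minor procedure, and the few-events argument does not carry over to that continuous outcome.
- A reader might take procedure to be the main driver of complications. Measuring Predictor Variables lists it as one of four factors. The sentence on balance points most directly to ASA class, smoking, BMI and radiation.
- A reader might suppose a material shift in the primary outcome. If a major case brought one extra visit, a gap of 15-20 points would move the visit difference by 0.15-0.20 of the planned one visit. The documents give no visit counts by procedure, so this is only an illustration under an assumption.
- A reader might infer bias or an inflated type I error. Randomisation remains valid.

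The Poisson model's covariates may also be set out in an analysis plan not shown here. The allocation scheme is different: this article describes it in detail, as a single list.

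**Conclusion.** The point holds as a minor, optional improvement. Procedure type is prognostic by the plan's own statement, a binary version of it is already needed, and the allocation does not use it. The imbalance frequencies rest on the assumed major share, and the small effect on complications rests on the assumed risk ratios; the documents supply neither. Stratifying would make the arms more comparable on a factor that readers will look at, and might add some precision for visits if procedure predicts them. It would do little for the precision of the complication comparison, and the net benefit analysis does not need it in the same way.

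**What to change.** 1. Before randomisation starts, list which planned operations count as major and which as minor. The protocol names the variable without defining it, so the list is also needed for the net benefit model. Patients consent before surgery, so the planned operation should be known when the envelope is issued.
2. Generate the ralloc sequence in those two strata, with two numbered envelope series, and issue the next envelope from the patient's stratum.
3. Include the stratum as a covariate in the Poisson regression of visits.
4. Replace the sentence on balance in the patient characteristics section with a statement that allocation is stratified on planned procedure and that ASA class, BMI and radiation will be described by arm.

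**Cost.** One option when the list is generated, a second envelope series, and slightly more handling. Two incomplete blocks could leave the arm totals up to 3 + 3 = 6 patients apart (39 and 33), against at most 3 with one list.
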